**Figure 3 F3:**
[figure not shown]
Flow diagram of the CaRe-ECMO program. First round of the CaRe-ECMO program refers to the protocolized cardiopulmonary rehabilitation delivery in the RCT part; second round of the CaRe-ECMO program refers to the protocolized cardiopulmonary rehabilitation delivery in the RCT part. Red flags symbolize measurement points of selective outcomes across all the follow-up time points. CaRe-ECMO, cardiopulmonary rehabilitation on extracorporeal membrane oxygenation; RCT, randomized controlled trial.

#### Control Group

No additional rehabilitation intervention, except usual care and ECMO therapy, will be provided to patients in the control group.

### Outcome Measures

#### Primary Outcome

The primary outcome of the CaRe-ECMO trial is the rate of ready for ECMO weaning at CaRe-ECMO day 7. It means that rate of ready for ECMO weaning will be calculated 7 days after cardiopulmonary rehabilitation delivery. Checklists to define ready for ECMO weaning (hereafter called ready for ECMO weaning checklists), either for VV-ECMO or VA-ECMO, have been prepared according to literature review and shown in Tables 5, 6 (20, 28). A fixed medical staff will be responsible for checkouts of listed items daily. Eligible patients defined as ready for ECMO weaning reveal the fulfillment of all the items in the checklists. Date of ready for ECMO weaning will be recorded and the rate of ready for ECMO weaning at CaRe-ECMO day 7 will be calculated.

**Table 5 T5:** Ready for VV-ECMO weaning checklist.

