## Abstract

**Background:** Mortality of patients suffering from critical illness has been dramatically improved with advanced technological development of extracorporeal membrane oxygenation (ECMO) therapy. However, the majority of ECMO-supported patients failed to wean from ECMO therapy. As one of several options, cardiopulmonary rehabilitation serves as effective intervention in the improvement of cardiovascular and respiratory function in various major critical illness. Nonetheless, its role in facilitating ECMO weaning has not yet been explored. The purpose of this study is to investigate the effectiveness of cardiopulmonary rehabilitation on rate of ready for ECMO weaning in ECMO-supported patients (CaRe-ECMO).

**Methods:** The CaRe-ECMO trial is a randomized controlled, parallel group, clinical trial. This trial will be performed in a minimum number of 366 ECMO-supported eligible patients. Patients will be randomly assigned to either: (1) the CaRe-ECMO group, which will be treated with usual care including pharmacotherapy, non-pharmacotherapy, and specific nursing for ECMO therapy and the CaRe-ECMO program; or (2) the control group, which will receive usual care only. The CaRe-ECMO program consists of protocolized positioning, passive range of motion (PROM) training, neuromuscular electrical stimulation (NMES), surface electrical phrenic nerve stimulation (SEPNS), and pulmonary rehabilitation. The primary outcome of the CaRe-ECMO trial is the rate of ready for ECMO weaning at CaRe-ECMO day 7 (refers to 7 days after the CaRe-ECMO program initiation). Secondary outcomes include rate of ECMO and mechanical ventilation weaning, total length in day of ready for ECMO weaning, ECMO weaning and mechanical ventilation, all-cause mortality, rate of major post-ECMO complications, ECMO unit length of stay (LOS) and hospital LOS, total cost for hospitalization, cerebral performance category (CPC), activities of daily living (ADL), and health-related quality of life (HRQoL).

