### Trial Objectives

The primary objective of the CaRe-ECMO trial is to investigate the impact of cardiopulmonary rehabilitation combined with usual care on rate of ready for ECMO weaning at CaRe-ECMO day 7 (refers to 7 days after the CaRe-ECMO program initiation), when compared to usual care alone. Secondary objectives are to evaluate the effects of cardiopulmonary rehabilitation on rate of ECMO weaning, total length of ready for ECMO weaning, total length of ECMO weaning, rate of weaning of mechanical ventilation, total length of mechanical ventilation, all-cause mortality, rate of major post-ECMO complications, ICU length of stay (LOS), total hospital LOS, total cost for hospitalization, cerebral performance category (CPC), activities of daily living (ADL), and HRQoL.

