### Interventions

#### CaRe-ECMO Group

Patients in the CaRe-ECMO group will be treated with usual care, ECMO therapy, and cardiopulmonary rehabilitation program. Usual care normally comprises pharmacotherapy, mechanical ventilation, continuous renal replacement therapy (CRRT), intra-aortic balloon pump (IABP), and specific nursing for ECMO therapy and their original injuries, as appropriate. In addition, patients will receive cardiopulmonary rehabilitation from a multidisciplinary team (e.g., clinicians, rehabilitation physicians, nurses, and therapists) who were fully trained to provide care to every ECMO-supported patient when medically appropriate. A core group of clinicians and therapists (e.g., XL, ZS, XC, YZ, YC, and SW) are competent in the use of a screening procedure (e.g., stability of hemodynamic and vital signs, stability of blood coagulation, stability of homeostasis, stability of mechanical ventilation, stability of ECMO flows, and stability of cannulation position and tightness) to determine appropriateness and safety for cardiopulmonary rehabilitation delivery according to the experience from the University of Maryland Medical Center (4). Detailed daily eligibility screening flowchart for cardiopulmonary rehabilitation is shown in Figure 2. Once the patients pass the screen, the therapists will proceed to provide protocolized cardiopulmonary rehabilitation program, which encompasses five evidence-based components according to literature review: (1) positioning; (2) passive range of motion (PROM) training; (3) neuromuscular electrical stimulation (NMES); (4) surface electrical phrenic nerve stimulation (SEPNS); (5) respiratory proprioceptive neuromuscular facilitation (PNF) techniques; and (6) airway clearance techniques (22–24). Detailed content and protocol are given in Table 4. It should be emphasized that hemodynamic and vital signs, ECMO flows, and cannulation position and tightness will be continuously monitored during each rehabilitation session. In case any adverse events occur, cardiopulmonary rehabilitation session will be discontinued. Corresponding reasons for discontinuous and exact length of therapy will be recorded.

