Respiratory PNF techniques	Manual thoracic expansion and compression	Therapist- or device-assisted pulmonary rehabilitation techniques	20 min per session 1 session per day	1. Improve chest wall compliance 2. Increase lung volume 3. Reduce and avoid atelectasis
Airway clearance techniques	Manual flutter mucus clearance	Therapist-, nurse- or device-assisted airway clearance techniques	20 min per session 1 session per day	1. Assist airway clearance 2. Reduce post-ECMO pulmonary complications (e.g., infection)
	High-frequency chest wall oscillation			
	Endotracheal suctioning			

*PROM, passive range of motion; NMES, neuromuscular electrical stimulation; SEPNS, surface electrical phrenic nerve stimulation; ICU, intensive care unit; PNF, proprioceptive neuromuscular facilitation*.

After randomized treatment, the primary outcome will be assessed at the CaRe-ECMO day 7 after last cardiopulmonary rehabilitation session. All the patients who are not responded (e.g., failure in fulfilling the criteria of ready for ECMO weaning and need continuous ECMO support), regardless of trial assignment, will be provided with open-label treatment of cardiopulmonary rehabilitation. Corresponding secondary outcomes will be assessed at the open-label stage according to the preplanned schedule.

Detailed procedure of the CaRe-ECMO program is shown in Figure 3.

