		**Study period**						
		**Eligibility**	**Allocation**	**Post-Allocation**			**Close-out**	
	**Timepoint**	** *–t_**1**_* **	** *t_**0**_* **	** *t_**1**_* **	** *t_**2**_* **	** *t_**3**_* **	** *t_**4**_* **	** *t_***x***_* **
		**Day of ECMO**		**7 days after CaRe-ECMO**	**14 days after CaRe-ECMO**	**30 days after CaRe-ECMO**	**90 days after CaRe-ECMO**	**Discharge day^*^**
Enrollment	Eligibility check	X						
	Informed consent	X						
	Randomization		X					
Assignment	CaRe-ECMO group		X					
	Control group		X					
Variables	Demographics		X					
	Clinical characteristics		X					
	Rate of ready for ECMO weaning			X	X	X	X	
	Rate of ECMO weaning			X	X	X	X	
	Total length of ready for ECMO weaning							
	Total length of ECMO weaning							
	Rate of mechanical ventilation weaning			X	X	X	X	
	Total length of mechanical ventilation							
	All-Cause mortality			X	X	X	X	
	Rate of major post-ECMO complications			X	X	X	X	
	Diaphragmatic thickness and mobility							
	ECMO unit LOS							X
	Total hospital LOS							
	Total cost for hospitalization							
	CPC			X	X	X	X	X
	ADL			X	X	X	X	X
	HRQoL			X	X	X	X	X

*CaRe-ECMO, cardiopulmonary rehabilitation on extracorporeal membrane oxygenation; LOS, length of stay; CPC, cerebral performance category; ADL, activities of daily living; HRQoL, health-related quality of life*.

* *Discharge day refers to discharge from ECMO unit and it may variate according to recovery process of patients*.

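### CaRe-ECMO day 7, the primary-outcome time point, is defined inconsistently and only by rehabilitation events, so control patients have no stated day 0

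*Protocol article*

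**What the plan says.** The protocol article describes the primary-outcome time point in several places.

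- **Abstract and Trial Objectives:** day 7 is "7 days after the CaRe-ECMO program initiation".
- **Primary Outcome:** the "rate of ready for ECMO weaning will be calculated 7 days after cardiopulmonary rehabilitation delivery". Whether delivery means its start or its end is not stated.
- **Interventions, CaRe-ECMO Group (text after Table 4):** "the primary outcome will be assessed at the CaRe-ECMO day 7 after last cardiopulmonary rehabilitation session".
- **Table 9:** the column for this visit reads only "7 days after CaRe-ECMO". Allocation is a separate, earlier column.

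On how the two arms reach that time point:

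- **CaRe-ECMO Group:** "Once the patients pass the screen, the therapists will proceed to provide protocolized cardiopulmonary rehabilitation program". The screen is repeated daily.
- **Control Group:** "No additional rehabilitation intervention, except usual care and ECMO therapy, will be provided to patients in the control group".
- **Statistical Methods:** readiness is analysed by Cox regression and Kaplan-Meier curves up to days 7, 14, 30 and 90, on intention-to-treat and per-protocol bases.
- **Interventions (same text after Table 4):** patients in either arm who are not ready at the day-7 assessment go on to open-label rehabilitation.

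**The concern.** A time-to-event or fixed-day comparison needs one time origin that exists for every randomised patient. Here each stated origin is something that happens after randomisation, and in one arm only.

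Three things are at stake.

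1. **Unequal windows.** If the rehabilitation arm is read 7 days after its first session and controls 7 days after allocation, any gap between allocation and first session is extra time in which to become ready.
2. **Patients with no clock.** A CaRe-ECMO patient who dies or becomes ready before a first session has no initiation date and so no day 7. A comparable control would presumably still be counted. That does not fit an intention-to-treat analysis.
3. **The switch to open-label treatment.** The day-7 result starts open-label rehabilitation in both arms. If a control's day 7 is undefined, so is the point at which that control can begin active treatment, and the day 14, 30 and 90 outcomes inherit the problem.

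**Working it through.** **Step 1: can the definitions be the same day?** Initiation and last session differ by the length of the course. For any course longer than one session, 7 days after initiation and 7 days after the last session are different days. The article does not state the course length, so the gap cannot be computed. The delivery wording in Primary Outcome is compatible with either reading, and the Table 9 label does not settle it.

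**Step 2: is there a control day 0 elsewhere?** Three places could suggest one.

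| Place | What it offers | Stated as the outcome origin? |
|---|---|---|
| Eligibility criterion 4 | 72 h of ECMO as a threshold | No |
| Blinding | a mimicked procedure for controls | No |
| Table 11 | a column for CaRe-ECMO Day 1, not limited by arm | No; Day 1 is not defined for controls |

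**Step 3: how much could a window mismatch matter?** The plan gives no figure for this, so what follows is illustration.

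Inputs from the article: 30% ready at day 7 and 174 per group before attrition (Sample Size Calculation); two-sided 5% level (Statistical Methods). I use 174 only as an arm size. It does not follow from the stated Cox inputs (the Schoenfeld formula for HR 0.5 and 80% power gives 66 events, and 66/0.30 = 220 in total), but that is a separate matter and this point does not depend on it.

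Assumptions of mine: constant hazard; no treatment effect; events counted from randomisation in both arms; the control window closes at 7 days and the CaRe-ECMO window d days later.

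Readiness in the CaRe-ECMO arm is p = 1 − 0.7^((7+d)/7).

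- d = 1: 1 − 0.7^(8/7) = 33.5%
- d = 3: 1 − 0.7^(10/7) = 39.9%

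The chance of a significant result from the pooled two-proportion test is Φ((D − 1.96·se0)/se1) + Φ((−D − 1.96·se0)/se1). Here D = p − 0.30, se0 = √(2·p̄(1 − p̄)/174) with p̄ = (0.30 + p)/2, and se1 = √((0.21 + p(1 − p))/174).

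| d (days) | D | se0 | se1 | False-positive rate |
|---|---|---|---|---|
| 0 | 0 | – | – | 5% |
| 1 | 0.0348 | 0.0499 | 0.0499 | 10.7% |
| 3 | 0.0992 | 0.0511 | 0.0508 | 49.2% |

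With 183 per group the last two rates are 11% and 51%. For scale, the planned effect is 30% to 45%.

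**Step 4: does another reading remove it?** Suppose both counting and risk start at the first session in the CaRe-ECMO arm and at allocation in controls. The windows are then equally long and, under a constant hazard, both arms read 30%. What remains is that patients ready or dead before a first session drop out of one arm only. Losing early recoveries would lower that arm's rate; losing early deaths would raise it.

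**The case against.** The strongest defence is that the term is defined once, in the Abstract and repeated in Trial Objectives, and that the other wordings are loose rather than contrary. On that view the Interventions sentence means assessment on day 7, after the first round's final session. This is a possible reading, but the sentence does not say it. Even if it is granted, the definition still rests on an event that controls never have.

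A second defence is that delays should be short. Criteria 4 and 5 require patients in both arms to be stable, fit for rehabilitation after 72 h on ECMO and free of contraindications. Enrollment, Randomization, and Allocation permits allocation only after eligibility is established. This stands, and it limits the likely size. A reader might infer that only the CaRe-ECMO arm is selected for stability, with immortal time always favouring it. The documents do not support that: the stability requirement applies to both arms before allocation, and the bias could run either way.

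A reader might also take the last-session wording to mean a full week's course plus a further week's wait, doubling the window. No course length is given, and the Abstract and Trial Objectives contradict that reading, so I attach no figure to it. Nor does the eligibility column of Table 9, headed by the day of ECMO, show a conflict with the 72 h criterion or criterion 8: a check begun on that day can be completed later.

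Finally, Figures 1 and 3 were not available to me and might mark a common start. They could not remove the disagreement between the written sections. An article may leave operational detail to a fuller protocol, but this one states the definition several times and the statements do not agree.

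**Conclusion.** The point holds as an inconsistency in the definition of the primary outcome and the lack of a stated control origin. Initiation and last session, taken literally, are incompatible anchors, and neither can be applied to controls. The arms can be compared over different windows; the text does not show that they will be.

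The size is not fixed by the documents. False-positive rates of about 11% (1 day) and 49% (3 days) rest on a constant hazard, 30% readiness at 7 days, no treatment effect and a hybrid clock that the article does not state. Under another reading the inflation disappears and only the differential loss of patients before a first session remains. The case for acting does not rest on those figures: the primary endpoint and the day-7 switch depend on a post-randomisation event in one arm, and the remedy is nearly free.

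**What to change.** - Set day 0 as the date and time of randomisation in both arms, and record it for every patient.
- Define the primary outcome as all checklist items fulfilled by 168 h (7 × 24 h) after randomisation, whether or when rehabilitation started.
- Count days 14, 30 and 90 from the same origin.
- Reconcile the Abstract, Trial Objectives, the Interventions text after Table 4, Primary Outcome and Table 9 to this definition. The statement on moving to open-label rehabilitation must be reconciled with it; when that treatment begins is for the trial team to decide.

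The cost is protocol wording and one date-time field. The sample size does not change. The downside is that a patient whose rehabilitation starts late has fewer treated days by 168 h, which dilutes the effect slightly. In return, every randomised patient has a day 7 and the intention-to-treat comparison is protected.

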**Ready for VV-ECMO weaning checklist**	
Move forward to the nest step when the former step is fulfilled, should all of the steps be fulfilled indication the patient is ready for ECMO weaning	
Step 1	The primary disease has been controlled or improved pulmonary function assessment: If VT < 6 mL/kg, FiO_2_ ≤ 60%, PEEP < 10 cmH_2_O, PaO_2_ > 70 mmHg, PaO_2_/FiO_2_ > 200 mmHg, PaCO_2_ < 45 mmHg, pH 7.35–7.45, improved changes in X-ray/CT scanning, lung compliance >0.8 ml/kg^*^cmH_2_O, then move to the next step
Step 2	Cardiac function assessment: If MAP > 70 mmHg, the heart rate increases over 20% of the baseline following the reduction of ECMO flow, then move to the next step
Step 3	Organ function and tissue perfusion assessment: If lactate < 2 mmol/L, SvO_2_ > 70%, no symptoms of respiratory distress and improved function of other damaged organs, then move to the next step
Step 4	Patient must tolerate a full weaning trial: If disconnect oxygen supply of the ECMO with no reduction of ECMO flow, observation for 6 h, monitoring the patient to maintain parameters mentioned in Step 1–3, then move to the next step
Step 5	If Step 1, 2, 3, and 4 are validated then the patient is under minimal ECMO support: Be sure that there is no CO_2_ retention and the patient can maintain normal oxygenation and normocarbia, and FiO_2_ reaches 21%, ECMO flow becomes 3–4L per minute and the sweep should be <1 L per minute, then move to the next step
Step 6	The patient is ready for VV-ECMO weaning

*VV-ECMO, venovenous extracorporeal membrane oxygenation; VT, tidal volume; FiO_2_, fraction of inspired oxygen; PEEP, positive end-expiratory pressure; PaO_2_, partial pressure of arterial oxygen; PaCO_2_, partial pressure of arterial carbon dioxide; MAP, mean arterial pressure; SvO_2_, mixed venous oxygen saturation*.

**Table 6 T6:** Ready for VA-ECMO weaning checklist.

**Ready for VA-ECMO weaning checklist**	
Move forward to the nest step when the former step is fulfilled, should all of the steps be fulfilled indicating the patient is ready for ECMO weaning	
Step 1	The etiology of cardiac failure must be compatible with myocardial recovery
Step 2	Pulmonary function should not be severely impaired: If FiO_2_ ≤ 50%, PEEP < 10 cmH_2_O, PIP < 30 cmH_2_O, PaO_2_ > 70 mmHg, PaO_2_/FiO_2_ > 200 mmHg, PaCO_2_ < 45 mmHg, pH 7.35–7.45, no pulmonary edema in X-ray/CT scanning, then move to the next step
Step 3	Hemodynamic and cardiac functional assessment: If MAP > 70 mmHg and PPD > 30 mmHg for 24 h, the heart rate increases over 20% of the baseline following the reduction of ECMO flow, VIS of <10, LVEF of more than 40%, aortic VTI of more than 10 cm/s, decreasing trend of cTnT and BNP values, CVP < 12 cmH_2_O, lactate < 2 mmol/L, SvO_2_ > 70%, with improved function of other damaged organs, then move to the next step
Step 4	The patient must tolerate a full weaning trial: Increase ACT to 200 s, then gradually reduce ECMO flow to 66% for 15 min, and then to 33% of its baseline value for 15 min, and finally a minimum of 1–1.5 L/min for 15 min. During the weaning trial, monitoring the patient to maintain parameters mentioned in Step 3
Step 5	The patient is ready for VA-ECMO weaning

*VA-ECMO, venoarterial extracorporeal membrane oxygenation; FiO_2_, fraction of inspired oxygen; PEEP, positive end-expiratory pressure; PIP, peak inspiratory pressure; PaO_2_, partial pressure of arterial oxygen; PaCO_2_, partial pressure of arterial carbon dioxide; MAP, mean arterial pressure; PPD, pulse pressure difference; VIS, vasoactive-inotrope score; VTI, velocity time integral; cTnT, cardiac troponin T; CVP, central venous pressure; SvO_2_, mixed venous oxygen saturation; ACT, activated clotting time*.

#### Secondary Outcomes

Secondary outcomes are listed and elaborated as follows:

1) Rate of ECMO weaning will be calculated according to date of ECMO weaning fulfilled.2) Total length of ready for ECMO weaning refers to exact length in day till patients fulfill all the criteria of ready for ECMO weaning according to daily checkout records (14).3) Total length of ECMO weaning refers to exact length in day for patients treated with ECMO therapy (29).4) Rate of mechanical ventilation weaning will be calculated according to date of mechanical ventilation weaning fulfilled. Daily screening of mechanical ventilation weaning will be strictly performed with checklist shown in Table 7 according to the American Thoracic Society and the American College of Chest Physicians Clinical Practice Guideline (30).5) Total length of mechanical ventilation refers to exact length in day for patients treated with mechanical ventilation.6) All-cause mortality is defined as rate of death due to any causes and will be calculated according to date of death (31).7) Rate of major post-ECMO complications refers to rate of complications occurred after ECMO including but not limited to ECMO-related complications (e.g., thromboembolism), mechanical ventilation-related complications (e.g., pneumonia), newly developed myocardial infarction, acute kidney injury, neurologic events (e.g., stroke, seizures), and multiple organ failure (32). Information of major post-ECMO complications will be collected in the Complication Recording Sheet (Table 8).8) Diaphragmatic thickness and mobility refer to ultrasound-guided evaluation of diaphragmatic thickness and mobility under M-mode (33).9) Extracorporeal membrane oxygenation unit LOS accounts for length in day for stay of patients in the ICU unit.10) Total hospital LOS accounts for total hospital LOS in day for stay of patients in both the ECMO unit and other departments.11) Total cost for hospitalization will be calculated by addition of the cost of all the units and department admission.12) Cerebral performance category will be recorded, for those successfully weaning of ECMO, to reflect post-ECMO neurological status (34).13) Activities of daily living will be evaluated, for those successfully weaning of ECMO, with Katz Index (35).14) Health-related quality of life will be measured, for those successfully weaning of ECMO, with SF-12 (36).

**Table 7 T7:** Mechanical ventilation weaning checklist.

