Upon the above rationale, the upcoming question is that what benefits of cardiopulmonary rehabilitation can be delivered to ECMO-supported patients. For clinicians, ECMO weaning is particularly challenging and annual ECMO mortality has been reported to be approximately ranged 40–70% (10, 11). According to our experience, delayed ECMO weaning also demonstrated worse functional prognosis and impaired health-related quality of life (HRQoL). Previous studies have documented that rate of mechanical ventilation weaning was improved in patients received early rehabilitation intervention, while its effectiveness in ECMO weaning remains unclear (12). Indeed, the successful weaning of ECMO is complex and multifactorial (13). ECMO weaning at the earliest possible time would be expected to improve outcomes, reduce cost, and optimize functional prognosis (14). This inspires us to hypothesize that if the medical rationale is based on its assumed benefits on cardiac function and oxygenation, then cardiopulmonary rehabilitation may subsequently contribute to earlier weaning of ECMO. Our perspective is to provide solutions with the application of cardiopulmonary rehabilitation and convert the aforementioned physiological changes (e.g., increased cardiopulmonary function) into patient-oriented outcomes (e.g., earlier weaning of ECMO and increased rate of ECMO weaning).

Considering the limited evidence in this aspect, ongoing innovation must move from guessing to exploring the effectiveness of cardiopulmonary rehabilitation through an adequately powered trial. Therefore, we design this multidisciplinary randomized controlled trial (RCT) to answer the following clinical question—can cardiopulmonary rehabilitation facilitate weaning of ECMO (CaRe-ECMO)? The results of this trial may subsequently provide innovative treatment solution, specifically the add-on effects of cardiopulmonary rehabilitation to the routine clinical practice for further successful weaning of ECMO.

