### Statistical Methods

The demographic and clinical characteristics collected at randomization will be presented as means with SDs or medians with interquartile ranges for continuous variables and as percentages for categorical variables, as appropriate.

For all the outcomes, we will estimate differences in effect size between the groups on both the intention-to-treat (ITT) and per protocol (PP) basis (39). Categorical variables will be compared with the chi-square or Fisher's exact tests and continuous variables will be compared with the Student's *t*-test or the Wilcoxon signed-rank test, as appropriate. The time effect of day the time-to-event outcomes identified (e.g., rate of ready for ECMO weaning, rate of ECMO weaning, rate of mechanical ventilation weaning, all-cause mortality, and rate of major post-ECMO complications) between the groups will be estimated with the Cox proportional hazards regression analysis and graphically illustrated using the Kaplan–Meier methods until CaRe-ECMO days 7, 14, 30, and 90, respectively (40). Variables, including total length of ready for ECMO weaning, total length of ECMO weaning, total length of mechanical ventilation, ECMO unit LOS, and total hospital LOS, will be treated with time-to-event data and will be analyzed with mixed-effects ordered logistic regression (41). Secondary outcomes with normal and non-normal distributions, including CPC, ADL, HRQoL, and diaphragmatic thickness and mobility, will be estimated for group differences with mixed-effects linear regression (41).

Considering that part of patients will definitely not reach the primary endpoint, i.e., ready for ECMO weaning at CaRe-ECMO day 7 for sensitivity purpose, we will assess the heterogeneity of the treatment effect on primary outcome and secondary outcomes in pre-specified subgroups of interest as per baseline data to be collected at randomization (e.g., age, gender, main diagnosis, comorbidities, the APACHE II score, ECMO mode, length since mechanical ventilation) by using exploratory *post-hoc* sensitivity adjusted analyses for any corresponding statistical methods mentioned above.

Interim analysis will be scheduled halfway through enrollment to check that there are no serious issues with respect to sample handling or data collection.

All the analyses will be conducted at a two-sided alpha level of 5% and will be performed using the Stata version 16 (StataCorp, College Station, Texas, USA) or other software, as appropriate.

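### ECMO, ventilation and length-of-stay outcomes count an early death as a short, favourable duration, and the planned ordered logistic model has no rule for death

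*Protocol article*

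**What the plan says.** In the protocol article, Secondary Outcomes, item 3 reads "Total length of ECMO weaning refers to exact length in day for patients treated with ECMO therapy". Item 5 is parallel: "Total length of mechanical ventilation refers to exact length in day for patients treated with mechanical ventilation". Item 9 is "Extracorporeal membrane oxygenation unit LOS accounts for length in day for stay of patients in the ICU unit", and item 10 is "Total hospital LOS accounts for total hospital LOS in day for stay of patients in both the ECMO unit and other departments". None of the four separates a count that ends by weaning or discharge from one that ends by death. Items 12 to 14 (CPC, ADL, HRQoL) are expressly limited to patients successfully weaned; the durations carry no such limit.

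Under Statistical Methods, the lengths "will be treated with time-to-event data and will be analyzed with mixed-effects ordered logistic regression". The same section applies both the intention-to-treat and the per-protocol basis to all outcomes, so patients who die stay in the intention-to-treat comparison. All-cause mortality (item 6) is a separate outcome and is not combined with any duration.

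Two further statements bear on the point. The Introduction says that "annual ECMO mortality has been reported to be approximately ranged 40–70" per cent. The Sample Size Calculation notes that ECMO patients generally remain in hospital until they are stable or have died, so death is an ordinary way for these counts to end.

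**The concern.** Under these definitions a patient who dies on ECMO after 4 days has an ECMO length of 4. A survivor weaned at day 10 has a length of 10. An ordered model on recorded lengths ranks the death as the better result, and the same happens with ventilator days, unit days and hospital days.

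If the programme prevents deaths, the patients it saves go on to add days to their own arm, and the four outcomes can read as harm. If it causes early deaths, they can read as benefit. The Introduction presents earlier weaning as a route to better outcomes and lower cost, and the Discussion ties the claim on practice to superior primary and secondary outcomes. A duration that points the wrong way would therefore be read as evidence on the trial's own question.

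**Working it through.** The protocol gives no figure to reproduce here, so the check has two parts: what the stated rules do to a death, and how large the effect could be.

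**What the rules do.**
- Items 3, 5, 9 and 10 give every patient a number of days, including those who die.
- Ordered logistic regression orders those numbers. It has no censoring and no competing event.
- With treatment as the only covariate, a proportional-odds comparison behaves much like a rank-sum test, so a rank test is a fair stand-in below.

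**Inputs.**
- From the documents: 183 per arm; mortality 40–70%; median ECMO length about 7 to 9 days (Discussion).
- Assumed, because the documents do not give them: the mortality difference between arms, and when deaths occur relative to weaning.

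**Model 1: constant daily hazards, same weaning hazard h in both arms.** With mortality on support m, the death hazard is h × m/(1 − m), and mean length is 1/(total hazard) = (1 − m)/h. With h = 0.05 per day:
- 50% v 40% mortality: 0.50/0.05 = 10.0 v 0.60/0.05 = 12.0 days
- 70% v 60%: 6.0 v 8.0 days
- 40% v 30%: 12.0 v 14.0 days

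The medians for 50% v 40% are 0.693 × 10.0 = 6.9 and 0.693 × 12.0 = 8.3 days, close to the protocol's 7 to 9. With h = 0.06, lengths rounded up to whole days and 183 per arm, repeated simulations of 2,000 to 3,000 trials had the rank test favour the higher-mortality arm at p < 0.05 in 32–34% of trials (50% v 40%), 44–47% (60% v 50%) and 22–24% (40% v 30%). Chance alone would give 2.5% in that direction.

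**Model 2: same weaning times in both arms, timing of death varied.** Weaning has a median of 8 days, so its mean is W = 8/0.693 = 11.54. Death on support has mean D = (median)/0.693. Mean length is m × D + (1 − m) × W. With median death at 3 days (D = 4.33) and mortality of 55% v 40%:
- higher-mortality arm: 0.55 × 4.33 + 0.45 × 11.54 = 7.6 days
- lower-mortality arm: 0.40 × 4.33 + 0.60 × 11.54 = 8.7 days

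Share of trials significant in the wrong direction, as the range over runs of 400 and 3,000 trials:

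| Median death (days) | 55% v 40% | 70% v 55% | 60% v 50% |
|---|---|---|---|
| 3 | 18–22% | 21% | 9–11% |
| 4 | 13–14% | 11–13% | 8–9% |
| 6 | 6–7% | 4–6% | 3–5% |
| 8 (as late as weaning) | 2% | 1–3% | 2% |

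The last row is chance: D = W, so mortality no longer affects the mean.

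The models differ in what they hold equal. Model 1 holds the daily chance of weaning equal, so any death removes days that would have followed. Model 2 holds fixed the weaning times of those who wean, so only deaths earlier than weaning matter. The documents do not say which is nearer the truth.

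**The case against.** The best defence has four parts.

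**The trial expects faster weaning, not only fewer deaths.** The plan has readiness rising from 30% to 45% by day 7. Taking readiness as a proxy for weaning (an assumption), the daily hazards are −ln(0.70)/7 = 0.051 and −ln(0.55)/7 = 0.085. With a control death hazard of 0.05, mean length is 1/0.101 = 9.9 days in control. In the treated arm it is 1/0.135 = 7.4 if the death hazard is unchanged, or 1/0.118 = 8.4 if it falls to 0.033. Mortality on support falls from about 50% to 37% or 28%, and length still shortens. This stands: reversal needs a mortality effect with little weaning effect. The smaller gap in the second case (9.9 v 8.4, not 7.4) shows that the bias against the arm with fewer deaths remains.

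**The mortality inputs are loose.** The cited 40–70% is general ECMO mortality, whereas enrolled patients must be stable after 72 h. Non-responders in both arms are offered open-label rehabilitation after day 7, so a sustained 10-point gap is uncertain. This also stands, and is why no single size can be claimed.

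**Weaning and death are analysed separately over time elsewhere.** True, and it limits the harm. It does not make the four lengths readable on their own.

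**Handling of death is detail for an analysis plan, and the article calls these lengths time-to-event data.** This does not stand. The article fixes both the definition and the model, and the named model does not do what that label implies.

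A reader might also infer more than the documents support:
- Item 2 may look like a fifth affected outcome. It is "exact length in day till patients fulfill all the criteria of ready for ECMO weaning", so death leaves it undefined, not short. Readiness is in any case planned by Kaplan–Meier and Cox methods to day 90.
- Total cost is also cut short by death, but cost up to death is a true cost, not a mis-scored outcome.
- The 72 h of ECMO before the programme, and earlier ventilation, add noise. Randomisation balances them in expectation, so they are not a bias.
- It might seem that no change of analysis could help. For items 3 and 5, weaning analysed with death as a competing event would.

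**Conclusion.** The concern holds for items 3, 5, 9 and 10. Followed as written, the plan ranks an early death as a short, favourable duration, and a mortality difference can bias all four against the arm with fewer deaths.

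The size is conditional on assumptions that the documents cannot settle. With equal weaning speed, deaths that cut support short, and mortality differences of 10–15 points, wrong-direction significance occurs in roughly 5–45% of trials. It falls to chance under Model 2 when deaths are as late as weaning, and need not occur if the programme also speeds weaning. It would be wrong to conclude that these outcomes will point the wrong way in this trial, only that they can. The primary outcome and its analysis are untouched, so this is a worthwhile correction to secondary outcomes, not a threat to the main result.

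**What to change.** Compare the arms on days alive and free of ECMO, of mechanical ventilation, of the ECMO unit and of hospital. Count from randomisation to day 30, and again to day 90, with death scored as 0 days. Analyse by proportional odds or a rank-sum test. For items 3 and 5, cumulative incidence of weaning with death as a competing event is an acceptable alternative. Keep raw lengths and cost as descriptive tables, split by survivors and non-survivors.

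The direction is then right under both models. Under Model 1 (h = 0.06, whole days), mean ECMO-free days to day 30 are 10.7 at 50% mortality and 12.0 at 40%. Under Model 2 they are (1 − m) × [30 − W × (1 − e^(−30/W))] = (1 − m) × 19.3, which gives 8.7 at 55% v 11.6 at 40%, and 5.8 at 70% v 8.7 at 55%.

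The cost is a change of outcome wording and a derivation from dates the trial already records. The downside is that the new outcomes mix survival with duration, so mortality and the raw lengths must be shown beside them.
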